#### Acupuncture group

According to the theory of TCM, insomnia is closely related to mental disorders [48]. Based on the conclusion of previous systematic reviews [49, 50] and our clinical experience, [51] we will select Baihui (GV-20), Shenting (GV-24), Yintang (GV-29), Shenmen (HT-7, bilateral), and Sanyinjiao (SP-6, bilateral). The location of acupoints will be determined in strict accordance with the National Acupoint Standard of the People’s Republic of China in 2006 (GB/T 12346-2006) (Fig. 3) [52].

**Fig. 3 Fig3:**
[figure not shown]
The location of acupoints

The subjects will be placed in the supine position, disposable sterile acupuncture needles with a length of 40 mm and a diameter of 0.30 mm will be selected (Huatuo, Suzhou, China), and the needles will be injected after disinfection. GV-20, GV-24, and GV-29 will be inserted 10 mm obliquely. HT-7 will be penetrated 10 mm straightly, while SP-6 will be perpendicularly punctured 15 mm. After piercing, thrusting and twirling will be used to achieve the sensation of “De qi.” After 30 min, take out the needle and squeeze it with a dry sterilized cotton ball. Subjects in the group which includes acupuncture will be treated 3 times a week for 4 weeks (Table 1).

**Table 1 Tab1:** Details of acupuncture interventions

Intervention	Acupuncture treatment
**Points**	Baihui (GV-20), Shenting (GV-24), Yintang (GV-29), Shenmen (HT-7, bilateral), Sanyinjiao (SP-6, bilateral)
**Depth description**	GV-20, GV-24, and GV-29 being inserted 10 mm obliquely. HT-7 being penetrated 10 mm straightly, while SP-6 being perpendicularly punctured 15 mm
**Needle retention time**	30 min
**Needle type**	0.30 × 40 mm (Huatuo, Suzhou, China)
**Needle stimulation**	By thrusting and twirling to achieve the sensation of “De qi”
**Frequency and duration of treatment sessions**	Three times a week for 4 weeks

#### TCM-eCBT-I group

TCM-eCBT-I is based on sleep health education, cognitive therapy, and sleep restriction, incorporating the Baduanjin exercise and five-element music. Under the guidance of professional IT staff and clinical psychologists, the TCM-eCBT-I has been well developed and tested in previous research (Table 2).
Sleep health education, cognitive therapy, and sleep restriction: [53, 54] provide daily guidance for the subjects in the form of a sleep management manual.Relaxation therapy of TCM: videos of Baduanjin exercise and five-element music will be sent to the subjects. Subjects are required to practice the Baduanjin exercise after 20:00 every evening, and listen to five-element music for half an hour before going to bed. This process will last for 4 weeks.

**Table 2 Tab2:** Details of the TCM-eCBT-I interventions

Intervention	TCM-eCBTI	Therapy method
**Session 1: Sleep health education**	Standard behavioral guidelines for lifestyle and environmental factors related to insomnia: [1] avoid drinking excitable drinks, such as coffee and strong tea, in the afternoon [2]; avoid drinking alcohol before going to sleep [3]; avoid eating too much before going to sleep [4]; keep the bedroom quiet and dark [5]; keep the room temperature appropriate [6]; regular exercise.	Push instructions in the form of the sleep management manual at fixed time daily. Record treatment participation by daily clock-in.
**Session 2: Sleep cognition**	Reduce excessive expectations and demand for sleep, correct one’s own bad suggestion, dispel the idea of controlling the sleep process, and weaken the excessive self-attention.	
**Session 3: Sleep restriction**	Estimate the actual sleep time according to last week’s sleep status: sleep efficiency more than 85%, increase sleep time by 15 min next week. Sleep efficiency is 80.00~84.99%, keep the sleep time next week unchanged. Sleep efficiency less than 80%, reduce sleep time by 15 min next week.	
**Session 4: Baduanjin exercise**	Reference to the new standing Baduanjin exercise	Guide the patients to exercise the Baduanjin exercise at home through online text animation and teaching video on the TCM insomnia system. Record treatment participation by daily clock-in.
**Session 5: Five-element music**	The music is selected from the *Five Elements of Tian Yun* published by the Beijing Higher Education Audio-visual Press. According to the classification of the patient’s condition, select music from the five tunes of Gong, Shang, Jue, Zhi, and Yu.	Five-element music is played online through the TCM insomnia system before going to bed. Meditation relaxation training is performed while playing music. Record treatment participation by daily clock-in.

The above content is enhanced by various interactive functions, including personalized goal setting, feedback based on self-reports, interesting animations, and sleep education videos. In addition, when recording sleep diaries online, the insomnia TCM system will automatically remind users to record their performance, which could also be used to evaluate subjects’ compliance. Daily timekeeping will be used to increase their participation and to encourage them to follow the plan [55].

#### Acupuncture combined with the TCM-eCBT-I group

The subjects simultaneously receive acupuncture treatment (the same as the acupuncture group) and TCM-eCBT-I treatment (same as the TCM-eCBT-I group). Subjects will be treated 3 times a week for 4 weeks of acupuncture, and TCM-eCBT-I will be performed for 20 min every night for 4 weeks.

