In the early stage, we developed the insomnia TCM system for chronic insomnia based on WeChat public platform (software copyright, registration number: 2019SR0900086), which is used for TCM diagnosis, information collection, and management of chronic insomnia. It includes modules such as sleep self-test, personal files, tracking, and health education. Baduanjin exercise is a popular traditional Chinese fitness method that combines physical movement, breathing, and psychological adjustment. By stimulating the meridians and organs, [37, 38] it can improve sleep. Five-element music guided by the basic theory of traditional Chinese medicine has a unique curative effect in treating insomnia [39]. We can make a comprehensive analysis according to the syndrome differentiation of patients and choose the corresponding treatment strategy [40, 41].

In order to take advantage of the unique advantages of traditional Chinese medicine in treating insomnia and to explore suitable eCBT-I for Chinese people, this study realizes eCBT-I based on the health education module of the insomnia TCM system, incorporating the Baduanjin exercise and the five-element music, to form TCM-eCBT-I. This study aims to construct a convenient and feasible TCM-eCBT-I, to combine the advantages of acupuncture and TCM-eCBT-I, and to explore the chronic disease management model of acupuncture in the treatment of chronic insomnia. Meanwhile, the short-term and long-term efficacy of acupuncture, TCM-eCBT-I, and acupuncture combined with TCM-eCBT-I will be evaluated to provide information for clinical decision-making. Our hypothesis is that acupuncture combined with TCM-eCBT-I is more effective than TCM-eCBT-I or acupuncture single therapy.

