## Trial status

This trial is recruiting patients now. Participant recruitment started on 20 October 2020 and is expected to end on 31 December 2021. This trial was registered in the Chinese Clinical Trial Registry on 17 May 2020. The registration number is ChiCTR2000032960. Protocol version 2, 31 March 2020.

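### The combined arm's TCM-eCBT-I is set at 20 min a night, yet it is said to be the same treatment that elsewhere requires half an hour of music plus an evening exercise

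*Protocol article*

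**What the plan says.** The section on the combined group describes its TCM-eCBT-I component in two ways:

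- By reference: patients receive "TCM-eCBT-I treatment (same as the TCM-eCBT-I group").
- By duration: "TCM-eCBT-I will be performed for 20 min every night for 4 weeks".

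The regimen being referred to is in the section on the TCM-eCBT-I group. That section builds the package from sleep education, cognitive therapy and sleep restriction, with Baduanjin exercise and five-element music as further parts. On the nightly activities it says:

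- "Subjects are required to practice the Baduanjin exercise after 20:00 every evening"; no length is given.
- Patients are to "listen to five-element music for half an hour before going to bed".
- "This process will last for 4 weeks".

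Table 2 lists one programme of five sessions. It contains no 20 min figure and no shortened version for the combined arm. For adherence it says: "Record treatment participation by daily clock-in".

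The Background gives the hypothesis that "acupuncture combined with TCM-eCBT-I is more effective than TCM-eCBT-I or acupuncture single therapy".

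**The concern.** The reference and the duration cannot both be followed. Someone who applies the TCM-eCBT-I group's regimen to a combined-arm patient exceeds 20 min with the music alone. Someone who keeps to 20 min does not deliver that regimen. The article does not say whether 20 min is a slip, the length of one component, or a total meant for both arms.

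This matters because combined versus TCM-eCBT-I is one of the two comparisons in the hypothesis. It isolates the effect of adding acupuncture only if TCM-eCBT-I is identical in the two arms. If 20 min were applied in the combined arm only, the contrast would estimate added acupuncture together with a smaller amount of TCM-eCBT-I. If less TCM-eCBT-I works less well, which is an assumption, this would count against the combination. If one duration is used in both arms, the contrast is not biased, but one of the two sections misdescribes the treatment and a reader cannot reproduce it.

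**Working it through.** **Inputs, all from the protocol article**

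| Item | Value | Section |
|---|---|---|
| TCM-eCBT-I per night, combined arm | 20 min | Acupuncture combined with the TCM-eCBT-I group |
| Music per night | 30 min | TCM-eCBT-I group |
| Baduanjin exercise per evening | *b* min, not stated, *b* ≥ 0 | TCM-eCBT-I group |
| Length of treatment | 4 weeks = 28 nights | both sections |

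**Step 1. Can the 20 min be reproduced?** The nightly time under the TCM-eCBT-I group's regimen is at least 30 + *b*, before any time spent on the daily manual. Setting 30 + *b* = 20 gives *b* = −10, which is impossible. No exercise length, including zero, fits the regimen into 20 min.

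**Step 2. Does another part of the article explain the figure?** Table 2 does not contain it. The only other 20 min duration is in Data collection and management, where it is the time for the online scale assessment, not treatment.

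**Step 3. Size of the gap in the text**

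- Per night: 30 − 20 = 10 min, a lower bound because *b* is left out.
- Over 28 nights, combined-group text: 20 × 28 = 560 min.
- Over 28 nights, TCM-eCBT-I group text, music only: 30 × 28 = 840 min.
- Difference: 840 − 560 = 280 min, and 280 / 840 = 33%.

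**Step 4. What this means between the arms**

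| What was done in practice | Difference in TCM-eCBT-I over 4 weeks |
|---|---|
| One duration in both arms | 0 min |
| 20 min in the combined arm only | at least 280 min |

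These are minutes of nightly activity. The article gives nothing that would convert them into PSQI points, so no effect on the primary outcome is derived.

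**The case against.** There is a fair case that this is a minor wording matter.

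- **The combined-group section does not conflict with itself in isolation.** Being the same as the other arm and lasting 20 min are compatible if both arms do 20 min. This is correct: the conflict arises because the reference points to a regimen that needs at least 30 min. It shows where the conflict lies but does not remove it.
- **The explicit statement on equivalence is that the component is the same.** There is one programme, one Table 2 and one online system, and no abbreviated version is described. A loose summary sentence or a drafting slip is therefore the more natural explanation. This stands, and it is why unequal dosing is not asserted here.
- **Twenty minutes may refer to one component**, such as the exercise or the manual-based guidance. This is possible as an intention. The sentence, however, attaches the figure to TCM-eCBT-I as a whole, and the package is defined to include the music.
- **The 280 min and 33% multiply a wording gap and could look like a dose effect.** They should be read only as the size of the discrepancy in the text, with a between-arm range that starts at 0.
- **The article does not say what the online system logs.** It mentions daily clock-in and timekeeping. Whether minutes are captured is unknown rather than ruled out.

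A fuller protocol may exist behind the article, but that does not answer the point. The issue is two stated durations that disagree, not detail left out.

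**Conclusion.** The concern holds. As written, the 20 min in the combined arm cannot be the same treatment as the TCM-eCBT-I group's regimen, and nothing in the article reconciles them. The discrepancy is at least 10 min a night and at least 280 min over 28 nights (33%), counting the music alone. The resulting difference between arms is 0 min if one duration is used in both, and at least 280 min if the sentence is applied literally to the combined arm only. The article does not show which applies.

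The direction of any bias, against the combination, rests on the assumption that less TCM-eCBT-I is less effective. The textual conflict itself needs no assumption. It should be corrected because it concerns the treatment delivered in a comparison on which the hypothesis depends, even though the likely cause is a drafting error.

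**What to change.** In the section on the combined group, delete or correct the 20 min. The sentence should say that TCM-eCBT-I is given exactly as in the TCM-eCBT-I group and Table 2: Baduanjin exercise after 20:00 and 30 min of five-element music before bed, each night for 4 weeks. If 20 min is the intended length of one component, or of the programme in both arms, state the length per component in the TCM-eCBT-I group section and in Table 2, and apply it to both arms.

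Then confirm from the patient materials and the online system what enrolled patients in each of the two arms were told, and report any difference. The clock-in records allow participation to be compared between these arms. They should not be relied on for minutes delivered unless the system is shown to record them.

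The cost is one corrected sentence and a check of instructions. Trial status says "This trial is recruiting patients now" and expects recruitment to end on 31 December 2021, while the article is dated 28 January 2022. If recruitment has closed, the correction and the check are still feasible. Sample size, outcomes and the planned analysis do not change.

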### Rescue medication

Throughout the whole trial, subjects will be told not to take any medicine or other treatment methods related to insomnia. If subjects suffer from insomnia all night, which seriously affects their work and life, they should take estazolam tablets (1 mg, Changzhou Four Drugs System, National Pharmaceutical Standard H32020699) temporarily under the guidance of researchers, allowing them to be used once a day for up to 3 days. The researcher will record detailed information (time, frequency, and dosage) of the drug use.

### Outcome measures

#### Primary outcome measures

The PSQI is a questionnaire to assess sleep quality. It consists of six aspects: sleep quality, sleep time, sleep efficiency, sleep disorders, hypnotic drugs, and daytime dysfunction. The total score of PSQI is 0–18 [56]. Sleep quality is negatively correlated with PSQI score. PSQI Chinese version has high reliability and validity and can be used as an effective tool for sleep screening and evaluation in clinical and scientific research [57, 58] PSQI > 5 points indicates that clinical treatment may be required [59] In this study, PSQI > 5 points will be used as the standard for chronic insomnia.

#### Secondary outcome measures

DBAS: Moran compiled the DBAS in 1993, which mainly includes five dimensions [60]: [1] beliefs about dysfunction of insomnia consequences, [2] belief that sleep is unpredictable and uncontrollable, [3] unrealistic sleep expectation, [4] misunderstanding of the causes of insomnia, and [5] misunderstanding of improving sleep style. A study shows that DBAS is not only used for qualitative assessment of sleep cognition, but also used as a tool to compare the efficacy before and after treatment [61] The Chinese version of the scale is also proved to have good reliability and validity [62].ISI: The ISI is a self-filling scale developed by Morin and Espie (1993), [63] which is mainly used to evaluate insomnia in clinical research [64]. It is used to evaluate the subjective feelings of insomnia. Subjects fill out the form according to their sleep status of the past week. The range of scores is 0–28. The severity of insomnia is positively correlated with the ISI score [65]. Chinese version of ISI has been used to evaluate Chinese insomniacs and proved to have high reliability and validity [66].Sleep diary: Subjects fill out a sleep diary for the night online after getting up in the morning, including the bedtime at night, the wake up time, the time to fall asleep, the number of times one wakes up after falling asleep, the feeling after waking up, the total sleep time, and the factors that interfere with sleep. Subjects can record their own sleep behavior patterns and daytime conditions affected by sleep through a sleep diary. Through the analysis by clinicians, they can intuitively grasp the sleep information of patients, which is of great significance for the diagnosis and evaluation of insomnia [67].HAMA: The HAMA was formulated by Hamilton in 1959 [68]. This test uses a 14-item version and 5-level scoring of 0–4 points and scores from both physical and mental aspects. The severity of anxiety symptoms is positively correlated with the HAMA score. Subjects with a clinical score of more than 21 are regarded as definitely anxious [69].HAMD: The HAMD was put forward by Hamilton in 1960. This study uses a 17-item version containing 7 factors, including despair, anxiety, somatization symptoms, and sleep disorders. The severity of depression is positively correlated with the HAMD score. More than 24 points indicate depression [70].FS-14: The FS-14 was proposed by Trudy Calder and other scholars in 1992. It consists of 14 items. The two dimensions of physical fatigue and mental fatigue are projects 1–8 and projects 9–14. The physical fatigue score is 8 points; the mental fatigue score is 6 points. The severity of fatigue is positively correlated with the FS-14 score [71].

### Safety assessments

Throughout the whole study, we will evaluate the safety through the table of adverse events [72]. The table should record the following elements for adverse events: time point, severity, measures taken, relatedness to treatment, time to normal, and time to symptoms and signs disappear. The adverse reactions of acupuncture mainly include local hematoma, dizziness, and blood stasis. If symptoms are seriously worsening, the treatment will terminate. No adverse effect of eCBT-I has been reported.

### Sample size

We adopted the PASS software method: this study was a randomized controlled trial, and the three groups were the acupuncture group, combined group, and CBTI group. The PSQI reduction rate of the subjects was the observed outcome index. According to the results of our preliminary test, it was expected that the effective rate of the acupuncture combined with TCM-eCBT-I group was 75%. The treatment rate of the acupuncture group was 65% and that of the TCM-eCBT-I group was 45%. The degree of certainty is 90%. The PASS15 software was used to calculate the total sample size of the three groups, *N* = 72 cases. Considering 20% of the cases of lost follow-up and rejection, a total of 90 cases were needed for the three groups, among which 30 cases were needed for each group.

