### Statistical analysis

The statistics and analysis of all data will be conducted by an independent researcher who does not participate in the experiment. We will use the SPSS 22.0 statistical software for data analysis. Descriptive statistics will be used to describe the demographic data of sample groups, while the normality of the distribution of each parameter will be checked by histogram and the Kolmogorov-Smirnov test. A chi-squared test will be used to assess the sample characteristics and gender.

The measurement data were expressed as mean ± standard deviation (SD) or median (interquartile range) [M (IQR)]. The analysis of variance will be used to test the between-group differences for the PSQI, ISI, DBAS, HAMA, HAMD, FS-14 scores, and sleep diary. As to the comparisons of the three groups, normality and homogeneity of variance are analyzed by variance analysis. If the variance is not uniform or normality is not conformed, the Mann-Whitney *U*-test will be used. Counting data is chi-square test. All statistical tests will be conducted bilaterally, and *P* < 0.05 indicates statistical significance. Data analysis will follow the intention-to-treat principle including participants who are randomly assigned. Missing data will be input with the last observation carried forward method.

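### The 90% behind N = 72 (90 recruited) rests on a PSQI reduction or effective rate that is not a listed outcome or named for any test, so it is unsupported for the planned PSQI score analysis; read as proportions, the rates do not give 72 either

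*Protocol article*

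**What the plan says.** All references are to the protocol article.

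- **Sample size.** "The PSQI reduction rate of the subjects was the observed outcome index". From a preliminary test, the plan expects that "the effective rate of the acupuncture combined with TCM-eCBT-I group was 75" per cent. For the other two arms: "The treatment rate of the acupuncture group was 65% and that of the TCM-eCBT-I group was 45" per cent. It adds "The degree of certainty is 90" per cent. PASS 15 gives a total of 72, raised to 90 (30 per group) for 20% loss. The section gives no significance level, named test, PSQI difference or SD.
- **Primary outcome measures.** The only primary outcome is the PSQI: "The PSQI is a questionnaire to assess sleep quality". The one threshold there, above 5 points, marks chronic insomnia and matches the inclusion criterion. It is not a response criterion.
- **Secondary outcome measures.** DBAS, ISI, sleep diary, HAMA, HAMD and FS-14. No responder or effective rate appears.
- **Statistical analysis.** "The analysis of variance will be used to test the between-group differences for the PSQI" and the other scales, with the Mann-Whitney test if assumptions fail. Count data get a chi-square test, with no variable named. Tests are two-sided at 0.05, by intention to treat, with last observation carried forward (LOCF).
- **Background.** "Our hypothesis is that acupuncture combined with TCM-eCBT-I is more effective than TCM-eCBT-I or acupuncture single therapy".

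**The concern.** The quantity that sized the trial is not one that the outcome list contains or that the analysis section assigns to a test. A power figure belongs to one outcome, one test and one assumed effect. Here the 90% is attached to a rate, while the primary analysis compares scores, and the article gives no PSQI difference or SD that would carry the figure across.

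What is at stake is how the result will be read. The hypothesis is that the combination beats each single therapy. A reader told that the trial had 90% certainty would take a non-significant combined-versus-acupuncture result as fairly strong evidence of no useful difference. The plan gives no basis for that.

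**Working it through.** **Inputs.** Rates 0.75, 0.65, 0.45; total 72, then 90; 20% loss (Sample size). Two-sided alpha 0.05 (Statistical analysis). Allocation 1:1:1 (Abstract and Study design). The 90% degree of certainty is taken to mean power, which is an interpretation.

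**1. The plan's own figures.** The loss adjustment reproduces: 72 / (1 − 0.20) = 90. The 72 was then tested against the stated rates.

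**2. Rates read as proportions, three-group chi-square (df = 2).**
- Mean rate = (0.75 + 0.65 + 0.45) / 3 = 0.6167.
- Squared deviations: 0.01778 + 0.00111 + 0.02778 = 0.04667; mean 0.01556.
- w² = 0.01556 / (0.6167 × 0.3833) = 0.01556 / 0.2364 = 0.0658, so w = 0.257.
- Noncentrality N·w²: 72 × 0.0658 = 4.74, power 48%; 90 × 0.0658 = 5.92, power 58%. Simulation gives 48.6% and 58.4%.
- For 90% power the noncentrality must be 12.65: 12.65 / 0.0658 = 192.3, so 193 subjects (195 in equal groups). For 80% power, 147.

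Pairwise on the same rates, at two-sided 0.05:

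| Contrast | n per arm for 90% power | Power at 24 per arm | Power at 30 per arm |
|---|---|---|---|
| 75% v 45% | 54 | 57% | 67% |
| 65% v 45% | 128 | 28% | 34% |
| 75% v 65% | 440 | 11% | 13% |

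Of the proportion-based variants tried (one- and two-sided; alpha 0.05, 0.10 and 0.05/3; 80% and 90% power), only one gives 24 per arm: 75% v 45% alone, one-sided alpha 0.10, 80% power. That conflicts with the two-sided 0.05 rule and covers one contrast.

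**3. Rates read as mean percentage reductions, ANOVA.**
- SD of the three means 75, 65, 45 around 61.67 = √(466.7 / 3) = 12.47 points.
- ANOVA with N = 72 has 90% power when Cohen's f = 0.4285.
- Implied within-group SD = 12.47 / 0.4285 = 29.1 points. At an SD of 25 power would be 97%, at 35 about 76%. The article states no SD.

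**4. What the fixed size delivers for the PSQI score.** No PSQI difference or SD is given, so only standardised effects can be stated.
- Three-group ANOVA, 90% power: f = 0.43 at N = 72; f = 0.38 at N = 90.
- Pairwise t-test (noncentral t), before any multiplicity adjustment:

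| n per arm | Detectable d, 90% power | Detectable d, 80% power |
|---|---|---|
| 24 | 0.96 | 0.83 |
| 30 | 0.85 | 0.74 |

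**5. One illustrative bridge from rates to scores (assumption).** Suppose the proportions arise from equal-variance normal scores cut at a common point. The probits are 0.674, 0.385 and −0.126, so d = 0.29 for combined v acupuncture and 0.80 for combined v TCM-eCBT-I, with f = 0.331. ANOVA power is then 69% at 72 and 79% at 90. Pairwise power is about 17% and 77% at 24 per arm, and about 20% and 86% at 30.

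**The case against.** **The rate may not be binary.** The section speaks of a reduction rate, an effective rate and a treatment rate, and mentions no responder. If 75, 65 and 45 are mean percentage reductions, the sized quantity is continuous, comes from the primary scale, and gives 72 at a plausible-looking SD. This stands as an ambiguity: a reader might infer that the trial was certainly sized on a responder endpoint, and the text does not prove that. But the SD is unstated, and percentage reduction is still neither the listed outcome nor the score named for ANOVA.

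**A chi-square test is planned for count data.** This is true, so it would go too far to say that the plan rules out testing an effective rate. What holds is narrower: no such rate is named as an outcome or assigned to that test, and if it were, power would be 48% to 58%.

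**The mismatch does not itself cost power.** This stands. Under the bridge in step 5, moving from proportions to scores raises power, from 48% to 69% at 72 and from 58% to 79% at 90. A reader might blame the whole shortfall on the switch of endpoint. On the proportion reading, it arises mainly because 72 does not follow from the rates.

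**The missing cut-off is detail.** Agreed. A responder definition is commonly left to the full protocol or analysis plan, neither of which is shown. A reader might infer that the threshold could be chosen after the data are seen; nothing in the article shows that, and the point does not rest on it.

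**Intention to treat with LOCF analyses 30 per arm, not 24.** This is correct, so both sizes are given. Neither supports the 90%.

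**Conclusion.** The point holds in this form: the 72 and the 90% are tied to a rate that is not a listed outcome and not named for any test, so they are unsupported for the planned comparison of PSQI scores. The chi-square and pairwise figures depend on reading the rates as proportions, the 90% as power, and alpha as two-sided 0.05. On that reading the stated size has about 48% power at 72 and 58% at 90, against about 193 needed for 90%. On the other reading, the figure rests on an SD of about 29 points that the article does not give.

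The stronger conclusion that the planned PSQI analysis is invalid or known to be underpowered does not follow. The test itself is unaffected, and its power cannot be computed without a PSQI difference and SD. The 69% and 79% are illustrations under an assumed normal shift. The statement should be corrected, but the trial need not be redesigned.

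**What to change.** Withdraw the 90% statement and rewrite the Sample size section for the PSQI score analysis that is planned, giving what the fixed size delivers:

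- ANOVA at two-sided 0.05: 90% power for Cohen's f of about 0.43 with 72 evaluable, or 0.38 with 90 analysed.
- Pairwise: detectable d of 0.96 (90% power) or 0.83 (80%) at 24 per arm, and 0.85 or 0.74 at the 30 per arm analysed under intention to treat with LOCF, stated as before any multiplicity adjustment.
- Convert these to PSQI points with the SD from the preliminary test, if it is available, so that readers can judge whether such differences are plausible.

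If the effective rate is kept, name it as a secondary outcome, assign it to the chi-square test and state its true power. On the present rates read as proportions, that is about 48% at 72 and 58% at 90. If the percentages are mean reductions, say so and give the SD used.

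Cost: one rewritten paragraph and, if the rate is kept, one outcome line. No more patients are needed. The downside is that the stated power becomes less favourable.
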